### Statistical methods

Statisticians are responsible for negotiating with major researchers to develop statistical analysis plans, establish databases, and conduct statistics with the SPSS statistical analysis system. All data will be collated by statisticians. The intention processing principle in SPSS 22.0 will be used for the data analysis. A unilateral test will be used for statistical results, and a *P* value < 0.05 will be considered statistically significant. The results will be expressed as the mean ± standard deviation. The t-test will be used for the normality and homogeneity of data, the hypothesis test of superiority will be used for major outcome indicators, the chi-square test will be used for normal distribution data, and the rank sum test or Fisher’s exact probability method will be used for non-normal distribution data. Statistical methods for the main efficacy indicators have been determined by the Capital Medical University statistical department.

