### Trial design

The trial is a single-center, prospective, randomized controlled trial (RCT) with a two-arm, parallel-group design (Fig. 1). Data analysis will be performed according to the superiority principle. The study will be carried out at Beijing Friendship Hospital and will be performed according to the principles of the Declaration of Helsinki (version Edinburgh 2000).

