### Outcome assessment

A blind observer from the Data Monitoring Committee (DMC) will collect all outcome data after surgery. The primary outcome of this study will be time to the first bowel motion by auscultation. The same surgical residents will listen to the bowel sounds every 4 h postoperatively. Time to first bowel motion is the duration until regular bowel sounds (more than two sounds every minute) are first heard after surgery [14].

The secondary endpoints will include the time to first flatus and time to defecation. This information will be obtained from participant questionnaires filled out once daily with the help of nurse staff. To observe changes in plasma brain–gut peptides, such as 5-HT, SP, VIP, gastrin, and CCK, we will collect venous blood from patients before the operation and on the first and third days after the operation. We will then centrifuge and freeze the plasma supernatant for later testing. We cooperate with our clinical experimental center to collect, code, centrifuge, freeze store, store, and test blood samples by a professional team. Secondary endpoints will also include VAS score of postoperative pain, vomiting and nausea, length of stay in the ICU, length and cost of stay in the hospital, as well as clinical complications such as fever, pneumonia, wound infection, and bleeding. Secondary outcome will be assessed by the medical team. The length of hospital stay is calculated as the number of days from the date of the operation to the date of discharge. Criteria for hospital discharge will include stable vital signs, the ability to tolerate solid foods after defecation without nausea or vomiting, and the occurrence of no other complications after the operation.

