### Sample size calculation

Due to a lack of related reports on the preventive usage of TEAS in patients undergoing GI surgery, we evaluated the effectiveness of TEAS according to our pre-experimental results. A priority-effectiveness test was used and the ratio between the groups was 1:1. According to the pre-experimental results, a difference in time to first bowel sounds of 12 h was thought to be clinically significant and selected as the effect size. This result in a hazard ration of 1.5. The COX regression sample size calculation formula was used to complete the sample size estimation. We set unilateral α = 0.05 and power = 0.90; PASS 2011 software was used for sample estimation and a total of 256 effective cases were estimated. According to the above sample estimation result and assuming 10% patient loss, a minimum of 280 cases is required. Therefore, we have set the required number of cases in this study to 280 cases, including 140 cases in the TEAS group and 140 cases in the sham TEAS group. Our General Surgery Department performs 400–500 cases of GI surgery per year; consequently, this study period is set at 2 years.

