In conclusion, the results of this methodologically rigorous trial are expected to provide not only clinical evidence of the effectiveness and safety of TEAS on GI function in patients after abdominal surgery but also demonstrate the mechanism of TEAS treatment on GI function.

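### The blanket one-sided P < 0.05 rule has no exception for complications, and neither way of reading it suits harms or supports the safety evidence the article expects

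*Protocol article*

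**What the plan says.** The decision rule is in Statistical methods: "A unilateral test will be used for statistical results, and a *P* value < 0.05 will be considered statistically significant". It names no outcome to which it does not apply. Trial design adds, for the analysis as a whole, "Data analysis will be performed according to the superiority principle". Statistical methods also ties superiority to a narrower group of outcomes: "the hypothesis test of superiority will be used for major outcome indicators". The same section names the chi-square test and Fisher's exact test, but allots them by whether data are normally distributed and not by outcome.

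Outcome assessment includes among the secondary endpoints "clinical complications such as fever, pneumonia, wound infection, and bleeding". Data collection methods and monitoring lists a safety analysis and the incidence of complications among the items to be recorded. Safety evaluation defines adverse events and how they are documented and followed, but gives no comparison between arms. The conclusion of the Discussion expects the trial to deliver "clinical evidence of the effectiveness and safety of TEAS on GI function in patients after abdominal surgery".

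**The concern.** A one-sided rule is a choice about which departure from no difference counts as evidence. For an efficacy endpoint in a superiority trial that choice can be defended. For complications the departure that matters most is the unfavourable one, and a test directed at benefit has no rejection region there: as the excess on TEAS grows, P moves towards 1. No difference, too little information and clearly worse would all be reported in the same way.

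This matters because the article announces evidence of safety and, in the Introduction, says the trial will inform whether TEAS should enter enhanced recovery protocols. If a non-significant one-sided P for complications were read as reassurance, it would feed into that decision without having tested for harm.

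**Working it through.** The article gives no complication rates and no figure for the comparison of complications, so there is nothing of that kind to reproduce. The counts below are assumptions. The 140 per arm comes from Sample size calculation.

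**1. Reading A: one-sided towards TEAS being better.** Fisher's exact test, 140 per arm:

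| TEAS events (assumed) | Sham events (assumed) | One-sided P (TEAS better) | Two-sided P |
|---|---|---|---|
| 28 (20%) | 14 (10%) | 0.994 | 0.029 |
| 21 (15%) | 7 (5%) | 0.999 | 0.009 |
| 35 (25%) | 14 (10%) | 0.9998 | 0.0015 |

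A doubling or tripling of the event count is not significant in every row under reading A, and is below 0.05 in every row on a two-sided test.

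**2. Reading B: one-sided P taken in the direction observed.** For 28 against 14 the one-sided P towards harm is 0.014, so the excess would be flagged. But each tail then rejects with probability 0.05 when there is no difference, so the nominal two-sided error is 0.05 + 0.05 = 0.10, not the declared 0.05.

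**3. Chi-square as named.** For 28 against 14 the pooled proportion is 42/280 = 0.15, and the statistic is 0.10² / (0.15 × 0.85 × 2/140) = 5.49, P = 0.019. This test rejects for harm as readily as for benefit. It is therefore two-sided in effect and does not match the unilateral rule in the same section.

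**4. What an interval would show.** For 28 against 14 the risk difference is 0.20 − 0.10 = 0.10. Its standard error is √(0.20 × 0.80/140 + 0.10 × 0.90/140) = 0.0423, so the 95% interval is 0.10 ± 1.96 × 0.0423, or about 1.7 to 18.3 percentage points. If both arms showed 10%, the half-width would be 1.96 × √(2 × 0.1 × 0.9/140) = 0.070, or ±7 points. The upper limit on the risk-ratio scale would be exp(1.96 × √(2 × 0.9/(140 × 0.1))) = 2.02. Even equal observed rates would therefore not exclude a doubling on the ratio scale.

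**5. Side check on the sample size.** The article states "We set unilateral α = 0.05 and power = 0.90" with a hazard ratio of 1.5 and arrives at 256 evaluable cases. Schoenfeld's formula for 1:1 allocation is 4(z_α + z_β)²/(ln 1.5)². If every evaluable patient has the event:
- two-sided 0.05: 4 × (1.960 + 1.282)²/0.1644 gives 256;
- one-sided 0.05: 4 × (1.645 + 1.282)²/0.1644 gives 209.

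The stated 256 is the two-sided figure under that assumption. The declared one-sided inputs would also lead to 256 if about 209/256 = 82% of patients had the event, but the article states no such rate. This is not part of the point. It shows only that wider two-sided reporting need not call for more patients.

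**The case against.** The strongest reply is that no sentence says complications are tested for superiority of TEAS. The explicit superiority clause covers the major outcome indicators, and would be redundant if superiority already governed everything. Chi-square, which a reader would expect for counts, is non-directional. Complications and adverse events are recorded whatever P comes out, and the safety sentence is closing prose and not a decision rule.

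Much of this stands, and it rules out several stronger readings that a reader might infer:

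- That the plan expressly tests complications for benefit only. The direction is an inference from the unrestricted one-sided rule and the general superiority statement.
- That non-significance is all the plan can yield on harms. Data collection methods and monitoring and Safety evaluation provide for recording complications and adverse events and for a safety analysis, and no section says safety will be concluded from a non-significant P.
- That the lack of a margin or upper bound is itself an error. That belongs to the statistical analysis plan, which is not shown.
- That the problem is low power. At assumed rates of 20% and 10%, a two-sided test with 140 per arm has power of only about 65%. That comes from the trial's size and would not be cured by changing sidedness.

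What the reply does not remove is the rule itself. It is stated, unrestricted, and unsuitable for harms on either reading. Pointing to chi-square replaces one difficulty with an inconsistency inside the section.

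**Conclusion.** The point holds as a defect of inference, not of recording. The one-sided rule as written reaches the complication endpoints. It either cannot flag an excess (P = 0.994 for an assumed 28 against 14) or runs at a 10% two-sided error, and the named chi-square test does not match it. A non-significant result under this rule cannot carry the evidence of safety that the Discussion expects.

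The counts are illustrative because the documents give no rates, but the conclusion does not depend on them: it follows from the direction of the test. The primary efficacy analysis is untouched. This is an inexpensive improvement in how harms are judged, and it does not challenge the trial's main result.

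**What to change.** In Statistical methods, restrict the one-sided superiority test to efficacy outcomes. Add that complications and adverse events will be reported as counts per arm and as the TEAS-minus-sham risk difference with a two-sided 95% confidence interval, in all randomised patients who started TEAS or sham. The population should be named because Discharge criteria lists a serious adverse event among the reasons for leaving the trial, and those patients must stay in the denominator. State that any conclusion on safety will rest on that interval and not on a non-significant P value.

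The cost is a short change of wording and one extra table from data already being collected, with no further patients or assessments. The downside is a more modest safety statement: with equal rates of 10% the interval would still span about ±7 percentage points.

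### The trial is sized by a Cox formula on a hazard ratio of 1.5, but the statistical methods state no time-to-event analysis, leave the primary test unnamed, and match chi-square and Fisher's exact tests to the wrong data type

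*Protocol article*

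**What the plan says.** The Outcome assessment section defines a time to event: "The primary outcome of this study will be time to the first bowel motion by auscultation". It is observed on a grid: "The same surgical residents will listen to the bowel sounds every 4 h postoperatively".

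The Sample size calculation section works on the hazard scale. It starts from a time difference, "a difference in time to first bowel sounds of 12 h was thought to be clinically significant and selected as the effect size", converts it ("This result in a hazard ration of 1.5"), and then says: "The COX regression sample size calculation formula was used to complete the sample size estimation". The inputs are one-sided alpha 0.05 and power 0.90. The results are 256 evaluable cases, raised to 280 for 10% loss.

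The Statistical methods section takes a different route. On reporting: "The results will be expressed as the mean ± standard deviation". On tests, after giving the t-test to normal data with equal variances: "the hypothesis test of superiority will be used for major outcome indicators, the chi-square test will be used for normal distribution data". Data that fail the normality condition get a separate rule in the same sentence: "the rank sum test or Fisher’s exact probability method will be used for non-normal distribution data". The section adds that a university statistics department has settled the methods for the main efficacy measures, without saying what they are, and that a statistical analysis plan will be developed. One-sided testing at 0.05 is repeated there.

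**The concern.** The quantity that justifies the sample size, a hazard ratio, appears in no stated analysis. The reporting rule and the t-test and rank-sum rules belong to fully observed continuous data. The primary outcome has only a hypothesis type (superiority), with no test statistic, model or effect measure.

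Two of the stated rules are wrong as written. Chi-square and Fisher's exact tests compare categorical outcomes; whether data are normally distributed does not decide between them or lead to either.

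Three things are at stake. The trial may estimate something other than what it was powered for. An unnamed primary test, in a trial that had already recruited 106 participants at this version, leaves room to choose after the data are seen. And a mean, a t-test or an ordinary rank-sum test cannot use a patient who withdraws or is removed before bowel sounds return, whereas a survival analysis uses that patient's follow-up up to that point.

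**Working it through.** **Inputs from the protocol article.** HR 1.5, 1:1 allocation, one-sided alpha 0.05, power 0.90, 256 evaluable cases (128 per arm), 10% loss, 280 total, 12 h difference, auscultation every 4 h.

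**Step 1: reproduce 256.** Schoenfeld's formula for 1:1 allocation, counting every evaluable patient as an event, is d = 4(z_α + z_β)² / (ln HR)², with ln 1.5 = 0.4055 and (ln 1.5)² = 0.1644.
- Two-sided 0.05: 4 × (1.960 + 1.282)² / 0.1644 = 255.7, so **256**. This is the protocol's figure exactly.
- One-sided 0.05, as stated: 4 × (1.645 + 1.282)² / 0.1644 = 208.4, so **209**.

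The 256 cases therefore correspond to two-sided 0.05 (one-sided 0.025), not to the alpha in the text. For the inflation, 256/0.9 gives 285 and 256 × 1.10 gives 282; the stated 280 is close to both.

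**Step 2: power of a Cox or log-rank analysis.** Power = Φ(½√d × ln HR − z_α). With d = 256, ½ × 16 × 0.4055 = 3.244.
- One-sided 0.05: Φ(3.244 − 1.645) = 94.5%.
- Two-sided 0.05: Φ(3.244 − 1.960) = 90.0%.

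With 252 events (280 less 10%) the figures are 94.2% and 89.6%.

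**Step 3: power of the rank-sum test, analytically.** Under proportional hazards with HR 1.5, the chance that a treated patient recovers before a control is 1.5/2.5 = 0.6. Then z = 0.1 / √((1/12)(2/128)) = 2.77.
- One-sided 0.05: Φ(2.77 − 1.645) ≈ 87%.
- Two-sided 0.05: Φ(2.77 − 1.960) ≈ 79%.

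**Step 4: simulation of all three tests.** 4,000 trials per setting, 128 per arm, HR 1.5, mean difference 12 h. Assumptions not in the protocol: Weibull times with shape 1, 1.5, 2 or 3 (implying control means of 36 to 95 h) and no censoring. Times were either exact or rounded up to the 4 h grid. The ranges below cover all eight settings.

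| Test | One-sided 0.05 | One-sided 0.025 |
|---|---|---|
| Log-rank | 94–95% | 88–90% |
| t-test | 90–94% | 84–89% |
| Rank-sum | 87–89% | 79–80% |

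The 4 h grid changes little. At the stated alpha the rank-sum test is about 6–7 points below log-rank and about 1–3 points below 90%. At the alpha behind 256 it is about 10 points below both.

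**Step 5: unobserved event times.** Patients may leave before the event through the 10% loss in Sample size calculation or the withdrawals and removals under Discharge criteria. The article gives no rate for leaving before the primary event, so this effect cannot be sized.

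**The case against.** The strongest reply is that this is a condensed article. The Statistical methods section gives the primary outcome its own clause, says its methods have been settled elsewhere, and announces an analysis plan. The t-test and rank-sum rules stand beside that clause and are not said to govern the primary outcome. The use of a Cox formula for sizing itself points to a Cox analysis. This stands in part: the article does not rule out a Cox model, so a reader who infers that the hazard ratio will never be estimated goes further than the text. It does not excuse the rules that are stated. A blanket mean ± SD suits a time-to-event outcome poorly, and the chi-square and Fisher assignments are wrong whatever a later plan says.

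A reader might also infer that the planned 90% power is lost. The documents do not support that in general. At the stated one-sided 0.05 the t-test reaches 90–94%, and the rank-sum test falls only slightly short. A loss of about 10 points needs both the rank-sum test on the primary outcome and the two-sided alpha that the text does not state.

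Finally, a reader might infer that the slowest recoveries will be dropped and bias the result. That is possible but not shown. The text does not say such patients will be excluded, it invokes an intention-to-treat principle (loosely worded), and nothing shows that those who leave are the slow recoverers. Discharge from hospital requires defecation and tolerance of solid food, so ordinary discharge should rarely precede the return of bowel sounds.

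**Conclusion.** The point holds as a mismatch between design and stated analysis. The sample size rests on a Cox model and HR 1.5; the stated methods contain no time-to-event method or hazard ratio and name no statistic for the primary superiority test. The matching of chi-square to normal data and Fisher's exact test to non-normal data is a plain error.

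The power consequence is conditional. If the rank-sum rule were used for the primary outcome, power would be about 87–89% rather than 94–95% at one-sided 0.05, or about 79–80% rather than 88–90% at two-sided 0.05. These figures assume proportional hazards at HR 1.5, 128 per arm and complete data. The point does not depend on them. The inability of mean-based and ordinary rank-sum analyses to use incomplete follow-up is a further reason for a survival method, of unknown size here. The stated one-sided alpha and the 256 cases also do not agree, since one-sided 0.05 needs only 209 events.

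**What to change.** Rewrite the Statistical methods section as follows.

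- **Primary analysis:** a Cox model or log-rank test of time from surgery to first regular bowel sounds, stratified by surgery type (gastric or colorectal), as the randomization is described. Report the hazard ratio with its confidence interval and Kaplan-Meier medians by arm. Censor at the last auscultation when no event has been seen.
- **Time to flatus and time to defecation:** the same method.
- **Other outcomes:** chi-square or Fisher's exact test for categorical outcomes; t-test or rank-sum test for continuous ones.
- **Alpha:** make the sidedness and the 256 cases agree. Either state two-sided 0.05 (one-sided 0.025), which 256 supports at 90% power, or keep one-sided 0.05 and state that 209 events are needed (209/0.9 = 233 after 10% loss) and that 256 events give 94.5%.

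The cost is wording only. No new data are needed beyond the time of the last auscultation, which the 4-hourly checks should already provide, and SPSS can run these analyses. The change should be dated before the outcome data are unblinded.

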### Data collection methods and monitoring

The statistical professionals are responsible for formulating the statistical analysis plan through consultation with the main researchers, establishing the database, and using the SPSS statistical analysis system for statistics. A comprehensive efficacy analysis was conducted in accordance with the program set, and the whole analysis set, demographic and other baseline characteristics, and other efficacy indicators were analyzed in accordance with the program set.

The DMC is consisting by a doctor in charge of data collection and sorting, a scientific research manager and a statistician. The doctor from the DMC will record the actual number of individuals enrolled, the cases of exclusion, demographic and other baseline characteristics, compliance analysis, safety analysis, incidence of complications and combined treatment, and comprehensive efficacy evaluation. The demographic characteristics, medical history, and treatment history of the patients will be described, including the comparison of age, gender, disease course, and disease condition at the time of enrollment. The scientific research management committee will have access to the final trial dataset. At the end of the study, the original data and results will be submitted to the scientific research management committee; they will be disclosed to the public after the results are published.

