#### Exclusion criteria

Exclusion criteria are as follows: (1) surgical incision or scar on the meridian of L14 / PC6 / ST36 / ST37; (2) local skin infection at acupoints; (3) upper limb or lower limb nerve injury; (4) a history of spinal surgery; (5) participation in other clinical trials within the past 4 weeks; (6) inability to understand the visual analog scale (VAS) score and numeric rating scale (NRS) score or to use patient-controlled analgesia (PCA); (7) presence of a pacemaker; (8) preoperative complications involving severe CNS diseases or severe mental diseases; (9) operations requiring enterostomy or conversion to open surgery; or (10) necessity of transfer to the intensive care unit (ICU) for treatment after surgery.

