#### Discharge criteria

Discharge criteria are as follows: (1) requirement for individuals to withdraw during the test; (2) violation of the test program; and (3) occurrence of serious adverse events (AEs).

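### The article applies intention-to-treat to the data analysis but assigns baseline and other efficacy data to the program set, so secondary efficacy results can leave out randomised patients with a poor course

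*Protocol article*

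**What the plan says.** All references are to the protocol article.

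- **Statistical methods:** "The intention processing principle in SPSS 22.0 will be used for the data analysis". No outcome is exempted.
- **Data collection methods and monitoring:** "A comprehensive efficacy analysis was conducted in accordance with the program set, and the whole analysis set". The same sentence goes on to baseline characteristics and ends: "other efficacy indicators were analyzed in accordance with the program set". Neither set is defined and neither is named as the deciding one.
- **Discharge criteria:** besides withdrawal at the patient's request, the reasons are "2) violation of the test program; and (3) occurrence of serious adverse events (AEs".
- **Exclusion criteria:** items 9 and 10 are "operations requiring enterostomy or conversion to open surgery" and "necessity of transfer to the intensive care unit (ICU) for treatment after surgery".
- **Interventions:** stimulation in theatre begins ahead of anaesthetic induction. Active intensity is set to what each patient can tolerate at most; the sham electrodes carry no current.
- **Outcome assessment:** secondary endpoints include "length of stay in the ICU", length and cost of hospital stay, and "clinical complications such as fever, pneumonia, wound infection, and bleeding".
- **Safety evaluation:** when an adverse event occurs, the physician has discretion over suspending observation, and every adverse event is followed until it is resolved or stable.

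**The concern.** An analysis plan cannot keep all randomised patients for the whole data analysis and also confine the secondary efficacy outcomes and the baseline table to a per-protocol set. Whichever sentence is followed, the other is broken.

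The choice matters because of who can be removed. Protocol violation, a serious adverse event, conversion to open surgery, enterostomy and ICU transfer all arise after treatment has begun, and several plausibly go with slow bowel recovery or a long stay. In a superiority trial, dropping such patients is not conservative: it gives up the balance that randomisation provided. If more slow patients leave the TEAS arm, TEAS looks better than it is; if more leave the sham arm, a real benefit can be hidden. A baseline table restricted to the same set would not show whether the arms were comparable as randomised.

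**Working it through.** **1. The statements side by side**

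| Item | Statistical methods | Data collection methods and monitoring |
|---|---|---|
| Comprehensive efficacy | intention principle | program set and whole analysis set, unranked |
| Other efficacy indicators | intention principle | program set |
| Baseline characteristics | intention principle | program set |

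The last two rows conflict. The first is unranked rather than contradictory.

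**2. Can the exclusions fall after randomisation?** Stimulation starts before induction, so allocation must be known by then. Conversion and ICU transfer become known later. Enterostomy may be planned or decided in theatre. Patients meeting items 9 or 10 can therefore already be randomised and treated. If ICU transfers are excluded, the ICU-stay endpoint has little or nothing left to measure.

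**3. Can removal differ between arms?** Under Randomization and blinding, the doctors giving the stimulation and the anaesthesiologists know the allocation, and only the active arm receives current. The article does not say that violations are judged blind. Unequal removal is therefore possible, but not shown.

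**4. How large could the effect be?** The article gives no removal rates, so these are illustrations under assumptions: no true effect, 140 per arm, exponential times to recovery, log-rank test at one-sided 0.05.

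*Illustration A* (2000 trials, median 36 h, 4-hour grid). 12% of each arm have a slow course, and only slow patients are removed. The share of an arm removed is 12% times the removal rate, for example 0.12 × 0.80 = 9.6%.

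| Slow patients removed, TEAS vs sham | Share of arm removed | Type I error, slow hazard one half | Type I error, slow hazard one third |
|---|---|---|---|
| none | 0 vs 0 | 0.045–0.048 (both cases) | 0.045–0.048 (both cases) |
| 60% vs 30% | 7.2% vs 3.6% | 0.074 | 0.096 |
| 80% vs 20% | 9.6% vs 2.4% | 0.112 | 0.198 |

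A repeat of the 80% vs 20% case gave 0.12 and 0.21. In repeat runs of the same model, removing 50% of slow patients from both arms gave 0.06, against 0.0575 with no removal. Unequal removal unrelated to recovery gave 0.057 and 0.043.

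*Illustration B* (4000 trials). Removed patients are drawn at random from the slower half of their arm.

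| Removed, TEAS vs sham | Type I error |
|---|---|
| 0 vs 0 | 0.049 |
| 5% vs 5% | 0.046 |
| 10% vs 10% | 0.043 |
| 5% vs 0 | 0.094 |
| 10% vs 0 | 0.150 |
| 10% vs 5% | 0.089 |
| 15% vs 5% | 0.176 |

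With unequal removal the apparent rate ratio rose from 1.00 to between 1.04 and 1.10. The Monte Carlo standard error, √[p(1−p)/R], is at most √(0.198 × 0.802/2000) = 0.009.

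**5. Does keeping everyone need more patients?** The Schoenfeld formula is d = (z_α + z_β)² / [0.25 (ln HR)²], with HR 1.5 and power 0.90.

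- Two-sided 0.05: (1.960 + 1.282)² / (0.25 × 0.1644) = 255.7, so 256, the article's figure.
- The stated one-sided 0.05: (1.645 + 1.282)² / 0.0411 = 208.4, so 209. That mismatch is a separate matter.

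Power is Φ(√(d/4) × ln 1.5 − z_α), assuming that every analysed patient has the event.

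| Analysed | One-sided | Two-sided |
|---|---|---|
| 280 | 0.960 | 0.924 |
| 252 (280 × 0.90) | 0.942 | 0.896 |

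Analysing all randomised patients needs no larger sample. The risk from the exclusions is mainly bias.

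**The case against.** Several points on the other side are sound and limit the finding.

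- **Discharge need not mean loss of data.** A reader might infer that a serious complication ends observation and removes the patient from the complication, length-of-stay and recovery analyses. The article does not say so. Discharge criteria is silent on data collection, and Safety evaluation makes suspension discretionary and keeps adverse events followed. The monitoring section has complications and exclusions recorded without tying that record to the program set. Under-counting of complications is therefore not established.
- **Complications are not described as serious.** Whether a listed complication would trigger discharge is left open.
- **The primary outcome is not shown to be per-protocol only.** Comprehensive efficacy is named for both sets. Reporting both is ordinary, and ranking them could be left to an analysis plan that is not shown.
- **The wording looks translated.** Per-protocol set and full analysis set are the natural readings, but the terms are undefined and the sentence can be parsed in more than one way.
- **The illustrations assume what drives them.** Removal must be both unequal and related to recovery. Intolerance is a weak reason for inequality, since intensity is set to each patient's own limit, and nothing links intolerance to slow recovery.

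What does not fall is the conflict over baseline and other efficacy indicators. That is a stated contradiction, not an omission, and no unseen analysis plan can satisfy both sentences. Following adverse events for safety also does not place those patients in the efficacy analyses.

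**Conclusion.** The concern holds in a limited form. The article contradicts itself on the analysis set for secondary efficacy and baseline data, leaves the two sets for comprehensive efficacy unranked, and combines this with discharge reasons and exclusions that can arise after randomisation. The secondary efficacy analyses can therefore leave out patients with a poor course.

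The size cannot be derived from the document. If removal is unequal and related to recovery, at the rates assumed above, the one-sided type I error for a time-to-event outcome is about 7% to 20% instead of 5%. If removal is equal, there is no inflation. These are not estimates of this trial's error rate, and they should not be read as applying to its primary analysis, which the article does not confine to the program set. The conclusion rests on reading the intention principle as intention-to-treat and the program set as the per-protocol set.

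**What to change.** 1. In Statistical methods and in Data collection methods and monitoring, state that all randomised patients, analysed as randomised, are the primary set for the primary outcome, all secondary efficacy outcomes and the baseline table.
2. Define the per-protocol set and label its analysis a sensitivity analysis.
3. State that outcome data continue to be collected and analysed after any discharge from the trial unless consent is withdrawn.
4. Reconcile Exclusion criteria (items 9 and 10), Discharge criteria, Outcome assessment and Safety evaluation with this, so that it is clear how patients with conversion, enterostomy, ICU transfer or a serious adverse event enter each analysis. The rules for stopping stimulation remain the sponsor's to settle.

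**Cost:** mostly wording, and no added sample size. Some further auscultation, daily questionnaires and blood samples would be needed in discharged patients, and the estimated effect may be slightly smaller. With 106 of 280 patients recruited at the time of writing, the change could still precede the analysis.
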